# DIgital Alcohol Management ON Demand (DIAMOND) feasibility randomised controlled trial of a web-based intervention to reduce alcohol consumption in people with hazardous and harmful use versus a face-to-face intervention: protocol

**DOI:** 10.1186/s40814-015-0023-1

**Published:** 2015-08-08

**Keywords:** Alcohol, Brief intervention, Digital intervention, Randomised controlled trial

## Abstract

**Background:**

“Hazardous and harmful” drinkers make up approximately 23 % of the adult population in England. However, only around 10 % of these people access specialist care, such as face-to-face extended brief treatment in community alcohol services. This may be due to stigma, difficulty accessing services during working hours, a shortage of trained counsellors and limited provision of services in many places. Web-based alcohol treatment programmes may overcome these barriers and may better suit people who are reluctant or unable to attend face-to-face services, but there is a gap in the evidence base for the acceptability, effectiveness and cost-effectiveness of these programmes compared with treatment as usual (TAU) in community alcohol services.

This study aims investigate the feasibility of all parts of a randomised controlled trial (RCT) of a psychologically informed web-based alcohol treatment programme called Healthy Living for People who use Alcohol (HeLP-Alcohol) versus TAU in community alcohol services, e.g. recruitment and retention, online data collection methods, and the use and acceptability of the intervention to participants.

**Methods:**

A feasibility RCT delivered in north London community alcohol services, comparing HeLP-Alcohol with TAU. Potential participants are aged ≥18 years referred or self-referred for hazardous and harmful use of alcohol, without co-morbidities or other complex problems. The main purpose of this study is to demonstrate the feasibility of recruiting participants to the study and will test online methods for collecting baseline demographic and outcome questionnaire data, randomising participants and collecting 3-month follow-up data. The acceptability of this intervention will be measured by recruitment and retention rates, automated log-in data collection and an online service satisfaction questionnaire. The feasibility of using tailored text message, email or phone prompt to maintain engagement with the intervention will also be explored. Results of the study will inform a definitive Phase 3 RCT.

**Results:**

Recruitment started on 26 September 2014 and will run for 1 year.

**Conclusion:**

The proposed trial will provide data to inform a fully powered non-inferiority effectiveness and cost-effectiveness RCT comparing HeLP-Alcohol with TAU.

**Trial registration:**

ISRCTN31789096.

## Background

Alcohol is the second biggest lifestyle risk factor for disease and premature mortality after smoking [1]. Alcohol misuse is estimated to cost the UK around £21 billion per year [2, 3]. This includes National Health Service (NHS) costs for treating accidents, assaults resulting from alcohol intoxication, conditions such as liver disease, cardiovascular disease and cancers, and the cost of alcohol treatment services. Societal costs include those associated with absenteeism, unemployment, family breakdown, road traffic collisions and crime.

These costs are mainly due to the large number of “hazardous and harmful” drinkers who make up approximately 23 % of the adult population; about 7.1 million people in England [4]. Hazardous drinkers are those whose alcohol intake is greater than government recommended limits (14 units a week for women and 21 units for men; or 2–3 units daily for women and 3–4 units for men). Harmful drinkers are those drinking more than recommended limits, and experiencing alcohol-related harm, but without symptoms of physical or psychological dependence. About 3.6 % of the population (1.1 million) people in England are dependent on alcohol.

People drinking at hazardous or harmful levels can respond well to a tiered approach to treatment [5]. Tier 1 is identification and brief advice (IBA), also known as screening and brief intervention (SBI). This may be conducted by a health professional in any setting, for example general practice or accident and emergency department (A&E). Identification is through the use of validated questionnaires such as the Alcohol Use Disorders Identification Test (AUDIT) [6], or shortened versions of AUDIT such as AUDIT Consumption (AUDIT-C) [7] or the Fast Alcohol Screening Test (FAST) [8]. Brief advice involves a short conversation about the risks of alcohol use at the current level, advice on reducing drinking levels and sources of self-help, usually supplemented with a leaflet [9]. Tier 2/3 treatments are provided at community alcohol drug and alcohol services, which offer more specialised treatment for people who need more than IBA, including extended brief intervention face-to-face, either individually or in groups, and complimentary therapies tailored to the individual. Tier 4 is detoxification and other treatment targeted at dependent drinkers with significant co-morbidities such as liver disease, severe mental health problems or multiple substance misuse.

IBA for hazardous and harmful drinking results in a significant and sustained reduction in alcohol consumption, which has been quantified in a meta-analysis by Kaner et al. [10] as a mean difference of −38 g of alcohol a week (CI −53 to −23 g) compared with control treatments. This translates to a reduction in average weekly intake of around four standard UK drinks (1 unit = 8 g alcohol). IBA is also likely to be cost-saving [11]. Despite this, not everyone who drinks at hazardous or harmful levels will find IBA sufficient to help them reduce their drinking and will need to access Tier 2/3 services.

There are enormous challenges in meeting demand for Tier 2/3 services, and estimates suggest only 6 to 10 % of people with problem alcohol use are accessing specialist treatment in England [4, 12]. Over the last several years commissioners of drug and alcohol services have faced a funding deficit [13]. This has inevitably resulted in a shortage of trained alcohol counsellors, with skills over and above the generic competencies that all primary care and A&E health care professionals need to provide IBA. In addition, hazardous or harmful alcohol use is recognised to be a relapsing and remitting condition so patients may need to access help repeatedly. Even if services are available, people may be reluctant to attend due to perceived stigma of having alcohol problems, or they may work and so cannot attend during working hours.

Online interventions could address these challenges. Internet use is widespread: 84 % of households in Great Britain having access to the internet, 76 % of adults use the internet every day and 58 % use a mobile phone to do so [14]. Online interventions are relatively inexpensive to set up, are convenient to access and provide anonymity, which is important to people with stigmatising conditions. A recent systematic review has shown that online interventions may be effective and cost-effective in treating hazardous and harmful alcohol use [15]. The feasibility of providing online interventions similar to Tier 2/3 community alcohol services has been demonstrated and also found to be acceptable to alcohol counsellors [16]. However, much of the research to date has looked at online interventions for IBA, largely in student populations. There are relatively few data demonstrating the effectiveness of extended brief intervention in adult populations of hazardous and harmful drinkers, and no data comparing face-to-face treatment with online treatment.

A fully powered Phase 3 randomised controlled trial (RCT) could address these gaps in knowledge, but there are recognised challenges with trials of web-based interventions, hence we propose to undertake a feasibility RCT first. The challenges include low engagement rates and attrition (non-use or fall-off in engagement with the intervention [17]), which limit their effectiveness, and high dropout rates (e.g. failure to complete follow-up questionnaires) seen in online trials [18]. There is also the potential for widening the digital divide, leading to health inequalities, as people from more deprived groups are less likely to have access to the internet and older people may have limitations in readiness and capacity to use online technologies [19, 20]. In light of these challenges, we feel that a feasibility study is required prior to applying for funding to carry out a Phase 3 RCT designed to test the hypothesis that supported access to an online alcohol intervention which mirrors treatment in community alcohol services is as effective, and more cost-effective, than traditional face to face treatments.

### Aims of the trial

The overall aim of this study is to determine the feasibility of conducting a RCT comparing supported access to a web-based Tier 2/3 treatment called Healthy Living for People who use Alcohol (HeLP-Alcohol) with usual care (face-to-face treatment in community alcohol services). The feasibility study will determine recruitment and retention rates and acceptability of the intervention; will test the online randomisation and data collection instruments at baseline and at 3 months; and will test methods to promote participant engagement with the intervention. We will also estimate health professional time involved in facilitating both arms of the trial. The outcomes of this feasibility study will inform a fully powered Phase 3 randomised controlled effectiveness trial and an economic evaluation.

## Methods

### Design

This is a randomised controlled feasibility trial.

### Setting

The London boroughs of Camden, Islington and Haringey have agreed to participate in the study, and we have recruited four community alcohol services to take part. Teams will be trained in good clinical practice (including trial paperwork, confidentiality, data management/clinical governance) and supported in recruiting and consenting participants.

### Population

We will recruit hazardous and harmful drinkers, identified using a validated screening tool such as AUDIT and referred from primary care, secondary care or self-referred, to community alcohol services.*Inclusion criteria*: patients are eligible to take part in the trial if they are aged 18 or over at time of screening; have a diagnosis of an alcohol use disorder using AUDIT criteria (score 8 or over); have a stable place of residence; provide informed consent for randomisation, treatment and follow-up; are willing and able to use a computer to access an online alcohol treatment programme.*Exclusion criteria*: patients are excluded from the trial if they have undergone treatment for substance use or primary drug dependence (excluding nicotine) in the previous 90 days; are already receiving help for an alcohol use disorder; have outstanding legal issues likely to lead to imprisonment; have severe physical dependency on alcohol (Leeds Dependence Questionnaire >20) or severe and complex co-existing physical or mental health problems, or are at risk of self-harm or suicide; are unable to consult in English without an interpreter; or if they are pregnant. If alcohol counsellors have concerns about a client regarding child protection issues or domestic violence, they will also be excluded. Patients without prior internet experience or without home access to the internet will not be excluded, but will be offered additional training as part of their facilitated access to the web-based alcohol treatment programme. All participants will be given information about local free or low-cost public internet access points, such as libraries, health centres and cluster rooms and local sources of support.

### Intervention

Supported access to HeLP-Alcohol, a modular, web-based alcohol treatment programme for people who drink at hazardous and harmful levels but who are not dependent on alcohol. HeLP-Alcohol is designed to be used over a 6-week period and has three evidence-based phases based on Motivational Interviewing, Computerised Cognitive Behavioural Therapy, and Relapse Prevention. Users can set up tailored text message or email prompts to help them achieve their drinking goals. Participants will also receive a weekly text message, email or phone call to encourage use of the website.

### Comparator

Treatment as usual (TAU) at participating community alcohol services.

### Recruitment

Clients will attend their assessment appointment with an alcohol counsellor as usual. If the alcohol counsellor considers the client meets the inclusion criteria for the trial (detailed above) they will discuss the trial with the client and provide written information and ask them to sign the consent form if they express interest in taking part. The client will be given a 24-hour “cooling off” period to decide whether or not to proceed.

### Data collection

If the client wishes to participate, they will be allocated a trial identification number linked to their email address and mobile phone number. All data will be collected anonymously online. All participants will be emailed a link to complete the baseline data collection questionnaires (see outcome measures, below). After they have completed the questionnaires, they will then be individually randomised by computer to the intervention or TAU. Those randomised to the intervention will be emailed a link to HeLP-Alcohol and those randomised to TAU will be directed back to their community alcohol service. All participants will be emailed another request for follow-up data collection 3 months after randomisation. For those participants who do not respond to the first email, there will be another two follow-up emails and then a phone call or text message request. See Fig. 1 for CONSORT participant flow diagram [21].

**Fig. 1 Fig1:**
[figure not shown]
CONSORT participant flow diagram

### Outcome measures

#### Primary outcomes

Recruitment as a percentage of eligible patients.Retention measured by completeness of online data collection for each arm at baseline and at 3 months as a percentage of patients randomised.

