### Statistical analysis

As this is a feasibility RCT, no hypothesis is to be tested. The aim of the trial is to determine estimates of recruitment and retention rates, to determine acceptability of the intervention and to provide parameters for the power calculation for a Phase 3 trial. Success criteria for recruitment and retention will be 84 and 75 %, respectively, as per the UKATT trial [30].

The analysis will be mainly descriptive. Descriptive statistics will be used to compare demographic characteristics of those completing each arm of the trial with those lost to follow-up. We will use multivariate logistic regression with robust confidence intervals (CI) to examine the impact of age, gender, ethnicity and deprivation level on these outcomes.

We will perform an analysis using regression of outcome on randomised group, adjusted for baseline value of outcome (for those outcomes measured at baseline) and other variables (age, gender, ethnicity and deprivation level) to compare the two arms using the following outcome measures at 3 months. Differences between the intervention and control groups for continuous variables with skewed distribution, e.g. alcohol consumption, will be log transformed, following a similar analysis to that by Wallace et al. [31]:Change in mean unit consumption of alcohol per week;Change in AUDIT score;Change in level of current psychological global distress score;Change in self-efficacy score;Acceptability of intervention using CSQ-8;Use of additional sources of support accessed during the trial period.

For the intervention group, we will examine adherence to the intervention, measured through automated recording of numbers of log-ins and numbers of pages visited at each log-in. We will conduct within-group analysis using linear regression to examine the impact of age, gender, ethnicity and deprivation on use of the intervention (number of log-ins, number of pages accessed, number of modules completed).

Missing data will be handled as follows:The primary analysis will be the mean difference in changes from baseline in all outcome variables between intervention and control groups at 3 months, using all available results but without imputation of missing data. Secondary analyses will include all randomised individuals by assuming that non-responders have no change in any missing outcome measures;For use of the intervention, data will be largely complete as automatically collected by the website.

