## Discussion

Hazardous and harmful alcohol use is a growing problem in the UK. Face-to-face treatment is only accessed by around 10 % of those who could benefit, for several reasons, of which the most important are lack of provision, stigma and inconvenience. We have developed a psychologically informed web-based alcohol programme which may help fill this gap in access, but its effectiveness, cost-effectiveness and equality of access compared with usual treatment in community alcohol services need to be ascertained in a fully powered RCT. The results of this feasibility RCT will provide useful evidence for commissioners of alcohol services as previous studies of web-based treatments for hazardous and harmful alcohol use have been conducted mainly online, for example, comparing websites with and without interaction or feedback [31].

Conducting a Phase 3 RCT to compare a web-based alcohol treatment programme with face-to-face community alcohol treatment is likely to face challenges, hence the need for the feasibility study. Recruitment and retention rates in the feasibility RCT will give an indication of the acceptability of the trial to patients with problem alcohol use. Other methods such as qualitative interviews may give a better idea of acceptability or otherwise, both of the trial and the intervention, and we aim to undertake a separate qualitative study with participants and alcohol counsellors in due course. However, it may not be possible to get the views of people who decline to participate in the trial as they are likely to decline to take part in a qualitative study as well. It is also not possible to determine the characteristics of those who decline to take part as we are not able to collect their demographic data if they have not consented to be in the study. However, we will have access to summary data for all clients seen by a service as the services collect this data for their own evaluations, so this may give us some indication of the characteristics of those who decline to participate compared with those who consent.

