It may be that potentially eligible clients do not wish to participate in a trial where there is a chance of being randomised to a website when they may have a preference for face-to-face counselling, or they may not have easy access to a computer, or feel confident using a computer. If they mention a reason for not participating when their alcohol counsellor discusses the trial with them, then we may pick this up from the qualitative interviews with counsellors.

Alcohol counsellors themselves may not find it acceptable to recruit people to a trial where they have a 50 % chance of being randomised to a website. The counsellors may only ask people who they think will be computer-literate, or may not ask those who they worry might disengage with the service if they are not seen face-to-face (selection bias). There may be other reasons why counsellors do not recruit potential recruits which may come out in the interviews, including time pressures and competing priorities.

We chose community alcohol services to as a recruitment setting because we expected that our target population would present to these services in sufficient numbers. However, as we are excluding hazardous or harmful drinkers who have co-morbidities or complex problems such as other substance misuse, eligible clients may not in fact present in sufficient numbers to recruit successfully from this setting.

As previously discussed, attrition from online programmes and online trials is a common problem [17]. We hope to overcome this using text message, email and telephone prompts as previous studies suggests such prompts can improve engagement [32]. We will also collect data on other sources of help accessed during the study, participants’ satisfaction with the intervention and estimates of health professional time for each arm, which will inform the main trial.

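### The recruitment success criterion is a bare percentage with an inconsistent denominator, so it can be met when recruitment falls far short of the aim

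*Protocol article*

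**What the plan says.** Under Primary outcomes, the protocol article measures "Recruitment as a percentage of eligible patients". Under Statistical analysis it sets the pass mark: "Success criteria for recruitment and retention will be 84 and 75 %, respectively, as per the UKATT trial". No number of participants and no monthly rate is attached to that criterion.

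An absolute aim does appear elsewhere: 200 participants (Sample size), over one year (Trial status), from four community alcohol services (Setting).

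Eligibility is defined under Population. Among the conditions for being eligible are that patients "provide informed consent for randomisation, treatment and follow-up; are willing and able to use a computer to access an online alcohol treatment programme".

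Under Recruitment, the counsellor first judges whether the inclusion criteria are met, and only then discusses the trial and asks for consent. A 24-hour period for reconsidering follows. Under Data collection, randomisation comes only after the online baseline questionnaires are complete.

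The Discussion treats the recruitment rate as a sign of how acceptable the trial is to patients. It also raises two risks: that "eligible clients may not in fact present in sufficient numbers to recruit successfully from this setting", and that "The counsellors may only ask people who they think will be computer-literate".

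**The concern.** Estimating the recruitment rate is a stated aim of this feasibility trial, and the result is to inform a Phase 3 trial of 1665 participants. Two different things need to be learned: what share of suitable clients will accept randomisation, and whether these services see enough suitable clients.

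A percentage of eligible patients cannot answer the second question, because a small numerator over a small denominator passes as easily as a large one over a large one. It answers the first question only if clients who say no stay in the denominator, and the article gives conflicting signals on that. Clients whom a counsellor chooses not to ask raise the same difficulty: nothing says whether they count as eligible.

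A report that follows the text as written could therefore declare recruitment successful when uptake was low, numbers were low, or both.

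**Working it through.** **Inputs.** Threshold 84% (Statistical analysis); aim of 200 (Sample size); 12 months (Trial status); four services (Setting); eligibility conditions (Population); order of events (Recruitment, Data collection).

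**1. The plan's own figure.** The 84% is taken from the UKATT trial. The article gives no inputs for it, so it cannot be reproduced. What can be tested is the rule: recruited / eligible ≥ 0.84.

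**2. What the aim implies.**
- Overall rate: 200 / 12 = 16.7 per month.
- Per service: 200 / (4 × 12) = 4.17, about 4.2 per month.
- Eligible clients needed to reach 200 at exactly 84%: 200 / 0.84 = 238.1.

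**3. Volume.** The smallest count that satisfies the rule, for several numbers of eligible clients in the year:

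| Eligible | Recruited | Rate | Share of the aim of 200 | Per month | Per service per month |
|---|---|---|---|---|---|
| 25 | 21 | 84.0% | 10.5% | 1.75 | 0.44 |
| 50 | 42 | 84.0% | 21% | 3.5 | 0.88 |
| 100 | 84 | 84.0% | 42% | 7.0 | 1.75 |
| 238 | 200 | 84.0% | 100% | 16.7 | 4.17 |

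All four rows pass. In the first row the 95% Wilson interval for the proportion is 65% to 94%, so the pass is also very imprecise. None of this depends on how decliners are counted.

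**4. Denominator.** Let *c* be the share of otherwise eligible clients who consent, and *r* the share of consenters who go on to be randomised.
- Decliners removed (consent is part of eligibility): rate = *r*.
- Decliners kept: rate = *c* × *r*.

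The first expression does not contain *c*, so it says nothing about willingness to take part.

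Illustration with 100 otherwise eligible clients and 50 decliners (*c* = 0.5):
- Removed: at most 50/50 = 100%. With *r* = 0.9 assumed, 45/50 = 90%. Both pass.
- Kept: at most 50/100 = 50%. With *r* = 0.9, 45/100 = 45%. Both fail.

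With *r* = 0.9 and *c* from 10% to 50%, the first rate stays at 90% while the second runs from 9% to 45%. To pass with decliners kept, *c* would have to reach 0.84 / 0.9 = 93%. The values of *c* and *r* are assumptions; the article gives neither.

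**5. Numerator.** Consent, the 24-hour period and the baseline questionnaires all precede randomisation, so recruited could mean consented or randomised. If it means consented and decliners are removed, the rate is 100% by construction. The retention outcome does not pick up losses between consent and randomisation, because its denominator is patients randomised.

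**The case against.** The strongest reply is that the article never says decliners are left out. The counsellor judges eligibility before raising the trial, so a client who declines has already been judged eligible. Using the rate as a sign of acceptability makes sense only if decliners are counted. The participant flow diagram, which might settle the matter, is not visible in the text reviewed, and exact screening counts are often left to a full protocol. This stands as far as it goes. A reader might infer that the denominator definitely excludes decliners; the documents do not support that. They show eligibility conditions that remove decliners if taken literally, and other text that keeps them.

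The reply also limits other inferences a reader might draw:
- *That the protocol has no absolute recruitment figure.* It has the aim of 200 in one year, and a shortfall would be visible. What is missing is any link between that aim and the success criterion.
- *That 84% is an automatic trigger for Phase 3.* The article speaks of success criteria and of results that inform the later trial.
- *That too few eligible clients is the authors' chief worry.* It is one of several listed, alongside client preference, computer access, counsellor selection and attrition.
- *That Phase 3 would take about 79 years* (1665 / 21 = 79.3). This holds only if Phase 3 used these four services alone at 21 participants a year, which no text says.

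Counsellor selection is openly acknowledged, and interviews are planned to explore it. Interviews will not supply a denominator, however. None of these replies touches the volume result in step 3.

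**Conclusion.** The point holds in two parts of different strength.

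The volume part is certain and needs no assumption: 84% of eligible patients can be met with 10.5% of the aim, so the criterion cannot detect the shortage that the Discussion warns of.

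The denominator part is an inconsistency within the article. Population, on one side, and Recruitment and the Discussion, on the other, support different counts. The difference is large enough to decide the result: up to 100% against at most 50% in the illustration, which assumes that half of otherwise eligible clients decline. The undefined numerator adds to it.

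The outcome, the eligibility conditions and the threshold are all fixed in this article, so this is a fault in what it states together and not a detail left to another document.

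**What to change.** 1. **Tie success to the protocol's own target.** Add to the 84% criterion: 200 randomised in 12 months, that is about 16.7 per month overall or 4.2 per service per month. Making the existing aim a pass mark is a choice, but it uses the protocol's own figure.
2. **Define the denominator.** All assessed clients who meet the inclusion and exclusion criteria other than consent and willingness to use the online programme, whether or not a counsellor approached them.
3. **Define the numerator** as participants randomised.
4. **Collect the counts** as anonymous tallies at the four services. These need no individual data on decliners, which the Discussion says cannot be collected. The article states that "we will have access to summary data for all clients seen by a service", but not that those data record every eligibility criterion, so they can serve only as a partial cross-check.

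The cost is a short text change and simple tallies. Because recruitment was already under way when the article appeared, counts for the months already past may be incomplete and should be labelled so. The reported percentage will probably be lower than on the literal reading.
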